## Abstract

**Background:**

Mastitis and accompanying pain have been associated with the cessation of breastfeeding. Mastitis is an inflammatory condition of the breast and may be a result of decreased immunity and a lowered resistance to infection. Mastitis affects up to one in five breastfeeding women with most episodes occurring in the first 6–8 weeks postpartum. Antibiotics are often used in the treatment of mastitis, but have not been popular or proven effective as a preventative agent. The WHO has highlighted significant concerns relating to adverse harms of antibiotic use with the production of antibiotic-resistant strains of disease organisms. Increasing research suggests that specific probiotic bacteria possess significant anti-inflammatory properties and supports their potential use as immunomodulatory agents. While animal studies have shown promising results in the use of probiotics for preventing mastitis, their use in human trials has had limited investigation. The aim of this study is to evaluate the effectiveness of oral probiotics for the prevention of mastitis in breastfeeding women.

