### Randomisation

Randomisation to either “probiotic” or “placebo” will take place immediately after consent within 72 h of birth. The randomisation schedule will be prepared and centrally administered by a researcher not involved in patient care. A computer random number generator will be used to prepare the randomisation schedule in blocks of 4 and 6, and stratified by the incidence of previous mastitis. The randomisation sequence will be concealed until all data has been collected. The participant and researcher will be blinded as to treatment allocation. Participants using the mobile phone application system (APProve-Lite) will be randomised via a central password-protected web-based application developed by the APProve clinical trial unit. Concealment for participants using the ‘standard’ approach (not the APProve-Lite system) will be via opaque, sealed envelopes.

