### Outcome measures

The primary outcome will be defined as the incidence of mastitis up to 8 weeks following birth as measured by:Clinical diagnosis of mastitis ORAt least two of the following breast symptoms: pain, redness/inflammation, lump/swelling AND at least one of the following systemic symptoms: flu-like symptoms (body aches, headaches and chills) or fever ≥38°C. These symptoms must be present for at least 24 h [43].

Secondary maternal outcomes will include breastfeeding duration (total/partial), recurrence of mastitis, development of breast abscess, cracked nipples, use of antibiotics, overall maternal health and well-being, breastfeeding support, number of doctor’s visits for probable mastitis, overall doctor’s visits, adverse effects of treatment, and incidence of primary mastitis between 2 and 6 months postpartum. Maternal lifestyle factors which may affect breastfeeding outcomes will also be assessed. Acceptability and compliance of the trial product and the APProve-Lite system will also be examined as well as preference for method of postnatal questionnaires.

Secondary infant outcomes will include growth (height and weight) and well-being in the first year of life (measured at 2, 6 and 12 months as assessed via self-report of health conditions including infections (gastrointestinal, respiratory), doctor’s visits, admission to hospital, allergic reactions and/or use of antibiotics.

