### Data collection

To assess the comparability of the study groups, baseline demographic and medical information will be collected at the time of entry into the study. The baseline assessment will include maternal age, socio-demographic data, smoking and alcohol use, infections during pregnancy, allergies, use of vitamins/supplements/probiotics in the previous month, history of prior pregnancies and lactations including previous mastitis and breastfeeding duration, and recent use of antibiotics. This information will be obtained from the participant and/or her medical record.

At the time of discharge, data related to the birth and infant feeding will be collected to evaluate the impact of events and outcomes around the time of birth on infant feeding practices. This information will be ascertained from both the participant and medical records and will include site, gestation at birth, mode of birth, antibiotics during labour, birth or postpartum, complications of birth, length of hospital stay and initiation of infant feeding. Baseline infant data on general characteristics and well-being will also be collected. This will include information on infant sex, birthweight, Apgar scores at 1 and 5 min, resuscitation and any morbidity and will be obtained from the infant’s medical record.

Follow-up questionnaires will be used to evaluate long term maternal and infant secondary outcomes as detailed above with timing and method of collected data presented in Table 1.

**Table 1 Tab1:** Timing of data collection for the APProve trial

Peripartum Period	Intervention	Timing
Birth (1–72 h)	Identification of eligible women	≥37 weeks’ gestation
	Patient information given, consent, baseline data collected	

Postnatal (Birth to 8 weeks)	Data collection of treatment compliance, breast pain, infection symptoms and infant feeding	Daily x 56 (APP/calendar diary)
	Data collection of well-being, Drs’ visits, and medication intake	Weekly x 8 (APP/email)
Postnatal (2,6 & 12 months)	Follow up questionnaire (post, email or APP)	2 months postpartum
	Follow up questionnaire (post, email or APP)	6 months postpartum
	Final follow up questionnaire (post, email or APP)	12 months postpartum

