### Statistical analyses

The analysis and reporting of the results will follow the CONSORT guidelines (http://www.consort-statement.org/). Primary and secondary outcomes will be analysed using an intention-to-treat approach, which includes all losses-to follow-up, non-compliances or withdrawals. Baseline characteristics will be compared between allocated treatment groups using frequencies and descriptive statistics. The principal analysis will use an unadjusted Chi-Square test to compare the incidence of mastitis between the two groups. The corresponding unadjusted relative risk with 95% confidence interval will also be calculated. Further analysis of the primary outcome will use multivariable logistic regression to examine the effect of adjusting for any imbalances at baseline or important predictors of mastitis (e.g. previous history of mastitis, antibiotic use, cracked nipples, or duration of breastfeeding). Additional unadjusted and adjusted analyses of all secondary outcomes will be performed using measures and multivariable models appropriate for the outcome. An analysis of women compliant with treatment (per protocol) will also be performed to assess the robustness of the primary findings. For all analyses, the number of cases with complete data and those with missing values will be reported. If necessary, reason for and type of missing data will be assessed to determine whether multiple imputation, sensitivity analysis or other approaches (“best” and “worst” case scenario, last value carried forward) will be required. Analyses will be performed using SPSS Version 24 (IBM SPSS Statistics, 2016 IBM Corporation, Chicago, IL) by an analyst not involved in any data collection and blinded to treatment allocation.

To assess the impact of the APP, the rate of primary and secondary study outcomes will be compared between the main study group and small sub-sample. Compliance rates in the ingestion of the intervention, and completeness and acceptability of data collected during daily and weekly follow-up will also be examined between the two study groups.

This protocol has been formatted according to the SPIRIT (Standard Protocol Items: Recommendations for Interventional Trials) guidelines (Additional file 1).

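### The adjusted model of the primary outcome offers three of the trial's own secondary outcomes as example covariates without limiting them to pre-randomisation values, so its odds ratio can miss the total treatment effect

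*Protocol article*

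**What the plan says.** All references are to the Protocol article.

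- **Statistical analyses, principal analysis:** "The principal analysis will use an unadjusted Chi-Square test to compare the incidence of mastitis between the two groups", with an unadjusted relative risk and 95% confidence interval.
- **Statistical analyses, further analysis:** a multivariable logistic regression of the primary outcome is planned "to examine the effect of adjusting for any imbalances at baseline or important predictors of mastitis". The examples given are "previous history of mastitis, antibiotic use, cracked nipples, or duration of breastfeeding".
- **Outcome measures:** "Secondary maternal outcomes will include breastfeeding duration (total/partial), recurrence of mastitis, development of breast abscess, cracked nipples, use of antibiotics".
- **Randomisation:** allocation "will take place immediately after consent within 72 h of birth".
- **Data collection:** the baseline assessment includes "history of prior pregnancies and lactations including previous mastitis and breastfeeding duration, and recent use of antibiotics". Antibiotics around labour and birth are also recorded, at discharge. Cracked nipples do not appear among the listed baseline items.

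**The concern.** Antibiotic use, cracked nipples and duration of breastfeeding are each named both as an outcome of treatment and as a possible covariate for estimating the effect of treatment on mastitis. A covariate measured after allocation can be changed by treatment, by the endpoint, or by both.

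The protocol itself supplies reasons to expect such links:

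- The abstract says "Antibiotics are often used in the treatment of mastitis", so antibiotic use can follow from the endpoint.
- The Background section reports that mastitis is associated with stopping breastfeeding, so duration may follow from it too.
- The Background section also names nipple damage as a risk factor and a route of entry for organisms, so cracked nipples may lie upstream of the endpoint.
- The Discussion expects that the probiotic may lengthen breastfeeding and reduce antibiotic use.

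Conditioning on a variable on the causal path removes part of the effect. Conditioning on a consequence of the endpoint that treatment also affects by another route can create an effect where there is none. The adjusted odds ratio will be read beside the chi-square result, and could then seem to contradict or reinforce it for reasons unrelated to whether the probiotic prevents mastitis.

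**Working it through.** **1. Status of each example covariate**

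| Covariate | Secondary outcome? | Baseline version listed? | Reading |
|---|---|---|---|
| Previous mastitis | No | Yes; also the stratification factor | Clearly pre-randomisation |
| Antibiotic use | Yes | Yes (recent use; labour and birth) | Ambiguous |
| Duration of breastfeeding | Yes | Yes (previous lactations) | Ambiguous |
| Cracked nipples | Yes | No | No listed pre-randomisation version |

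The selection rule is "adjusting for any imbalances at baseline or important predictors of mastitis". The word for baseline attaches to imbalances; predictors are a separate category with no timing restriction.

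**2. Inputs for the illustrations**

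The Sample size section gives 18% mastitis in controls and a 50% reduction, hence 9%. These inputs reproduce the stated total of 452. With pooled variance, two-sided 5% and 80% power, n per arm = [1.960·√(2·0.135·0.865) + 0.842·√(0.18·0.82 + 0.09·0.91)]² / 0.09² ≈ 225.1, rounded up to 226, and 2 × 226 = 452. The point made here does not alter that figure.

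All covariate rates below are assumptions; the protocol gives none. Adjusted odds ratios come from a logistic model with treatment and the covariate as main effects, fitted to the exact cell probabilities.

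Unadjusted OR for 9% v 18%: (0.09/0.91)/(0.18/0.82) = 0.0989/0.2195 = 0.45.

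**3. Cracked nipples carry part of the effect**

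Assume 40% on placebo and 25% on probiotic, with tripled mastitis risk.
- Placebo: 0.60p + 0.40·3p = 1.8p = 0.18, so the risks are 0.10 without and 0.30 with cracked nipples.
- Probiotic: 0.75p + 0.25·3p = 1.5p = 0.09, so the risks are 0.06 and 0.18.
- OR without cracked nipples: (0.06/0.94)/(0.10/0.90) = 0.57.
- OR with cracked nipples: (0.18/0.82)/(0.30/0.70) = 0.51.
- Adjusted OR: **0.54**, against 0.45 unadjusted. With 40% v 20% it is 0.59.

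Extreme case: the whole effect runs through cracked nipples (40% v 20%, risks 0.10 and 0.30 in both arms). Probiotic risk = 0.8·0.10 + 0.2·0.30 = 0.14. Unadjusted OR = (0.14/0.86)/(0.18/0.82) = 0.74; adjusted OR = **1.00**.

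**4. No effect on mastitis, but treatment changes other antibiotic use**

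Assume 18% mastitis in both arms, antibiotics in 80% of cases in both arms, and antibiotics in 5% of non-cases on placebo and 3.5% on probiotic.
- OR among antibiotic users: 0.05/0.035 = 1.43.
- OR among non-users: 0.95/0.965 = 0.98.
- Adjusted OR: **1.16**, against 1.00 unadjusted. With 2.5% on probiotic it is 1.31.
- Exchanging the arms inverts the result: 1/1.16 = 0.86, an apparent benefit.

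If instead 80% of placebo and 60% of probiotic cases receive antibiotics (10% of non-cases), the stratum ORs are 0.75 and 2.0, and the adjusted OR is about 1.2.

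**5. No effect on mastitis, but treatment changes stopping breastfeeding**

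Assume 30% of cases stop in both arms, and 20% of non-cases stop on placebo against 14% or 10% on probiotic. The adjusted OR is about 1.04 or 1.09.

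**6. Antibiotic use depends on mastitis only**

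With 80% of cases and 5% of non-cases treated in both arms, the antibiotic rates cancel from each stratum odds ratio. The adjusted OR stays at **0.45**.

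**The case against.** The best defence has five parts.

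- **The covariates are only examples.** They are introduced as such and joined by an alternative, so none is fixed in the model. This stands. A reader might infer that the adjusted estimate is biased; the protocol does not support that. The estimate can be biased, if post-randomisation values are entered and treatment affects them in the relevant way. Step 6 shows a case with no bias.
- **A baseline reading is available.** For antibiotic use and breastfeeding duration this stands: the defect is ambiguity, not demonstrated conditioning on outcomes. It does not help cracked nipples. A statistical analysis plan that is not shown may settle the timing, but the list as published would lead it the wrong way.
- **The principal analysis is untouched.** This stands fully. A reader might infer that the trial's main conclusion is at risk. It is not: the chi-square test and relative risk use no covariates, and the adjusted model has no stated decision role.
- **The illustrations rest on unsupported inputs.** Partly right. No probiotic effect on cracked nipples is stated. Under double blinding with matched sachets, an 80% v 60% difference in treating established cases is hard to motivate, which is why step 4 leads with other antibiotic use. The move from 0.45 to 0.54 is also small beside sampling error. With 300 per arm and 54 v 27 events, SE(log OR) = √(1/27 + 1/273 + 1/54 + 1/246) = 0.252, giving a 95% interval of about 0.28 to 0.74. The figures show what is possible, not what is likely.
- **Mastitis is not shown to shorten breastfeeding.** Correct: the Background section reports an association, and no more is relied on here.

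A reader might also want adjustment for observed baseline imbalances struck out. That is a separate and debatable matter: it does not condition on post-randomisation variables, and no harm from it is shown here.

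**Conclusion.** The point holds in a limited form. Three of the four example covariates are the trial's own secondary outcomes, and the model is not confined to values from before randomisation. The problem is firmest for cracked nipples; for the other two it is a matter of unclear wording.

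If in-trial values are used, the adjusted odds ratio does not in general estimate the total effect of the probiotic. Its error may be nil, may attenuate a real effect or may produce an apparent effect under the null. The sizes shown depend wholly on the assumed covariate rates and on how treatment affects each covariate.

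Because only a supplementary analysis is affected, this should be fixed but does not threaten the primary test.

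**What to change.** Reword the covariate sentence in Statistical analyses:

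- Limit the adjusted model to variables measured before randomisation and named in advance: previous mastitis and, if wanted, baseline items already collected, such as recent antibiotic use and previous breastfeeding duration. The latter needs a coding rule for first-time mothers.
- Remove cracked nipples, and the in-trial values of antibiotic use and breastfeeding duration, from the covariate list.
- Analyse those three as the secondary outcomes they already are. If their role in the mechanism is of interest, place them in a separate mediation analysis labelled exploratory.

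The cost is about one sentence in the protocol or analysis plan, settled before unblinding. It needs no new data and changes neither the sample size nor the principal analysis.

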### Hypotheses

The primary hypothesis is that regular ingestion of the probiotic *Lactobacillus Fermentum* CECT5716 by women in the first 2 months following birth will decrease the incidence of mastitis in breastfeeding women.

The secondary hypotheses are that exposure to probiotics may also confer a benefit to breastfeeding mothers and reduce risk of infection among infants, particularly gastroenteritis. Furthermore, that the use of a mobile phone application system will provide a novel means of interacting with participants and improve participant compliance, completeness of data collection and reduce recall bias.

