### Intervention

The participant will be given an 8 week supply of her allocated treatment. The probiotic sachets and placebo sachets will be identical in every respect except for the *Lactobacillus Fermentum* CECT5716 (1 × 10^10^ CFU/mL) ingredient contained in the probiotic. Participants will be advised to take one sachet daily, preferably at the same time each day for a period of 8 weeks following the birth of her baby. As it is recommended to store the product below 25 °C, participants will be asked to refrigerate the boxes of sachets at home. The contents of the sachet should be mixed with water, juice or milk, stirred and consumed immediately. Women will be advised not to make up for missed doses by double-dosing, but rather to continue their daily routine as soon as possible. The number of unused sachets will be collected by the research coordinator at the end of the 8-week period.

Participants will be encouraged to maintain routine health care. If antibiotics are prescribed, women will be encouraged to continue with their treatment regime, but advised to take the treatment sachet at least 2 h after taking the antibiotic.

Participants using the APProve-Lite system (APP) will receive daily questionnaires collecting data on treatment intake, breast pain, infection symptoms and infant feeding. Weekly questionnaires will collect data on maternal and infant well-being, unscheduled doctor’s visits, and medication intake. Women not using APProve-Lite will receive an 8-week calendar diary to record their daily responses, along with a weekly questionnaire accessed by an emailed web-link.

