### Independent assessment of intervention and mobile phone application system

A separate sub-study will be conducted to assess the independent effect of the probiotic without the potential influence of the APProve-Lite system. Despite the APP being a tool to facilitate data collection and improve compliance, it may be viewed as an intervention in itself, and have an unintended effect on study outcomes. Assessment of the APP is important to ensure this tool does not bias or exert any influence on study outcomes. This will involve a sub-study utilising a pragmatic and ‘standard follow-up’ approach to data collection and follow-up of women throughout the trial for collection of information on symptoms related to study outcomes and ensuring compliance with the ingestion of the intervention.

The sub-study will involve a sample of 100 women who will be recruited on randomly selected days of each month. These women will be recruited and enrolled into the trial in an identical way to those of the APP group and randomised to the intervention as in the main study. However, they will not be asked to use the APP throughout the trial. Rather, these women will be provided with a 2-month calendar diary to complete each day. They will be encouraged to place this in a visible location such as on the fridge to encourage daily compliance. Here they will record daily ingestion of the probiotic and symptoms via check boxes (daily survey). They will be provided with an addressed reply-paid envelope in which to post the completed diary back to the recruiting center. Each week, women will be emailed a link to an online Survey Monkey questionnaire to complete (weekly survey). At the end of the intervention, women will be emailed a web-link to the 2, 6 and 12-month follow-up questionnaires.

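### The APP v diary comparison mixes a real APP effect with a difference in recording for symptom-defined mastitis, does not tie compliance to the sachet count, and has no measure of recall bias

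*Protocol article*

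**What the plan says.** Under Hypotheses, the protocol article expects the APP to "improve participant compliance, completeness of data collection and reduce recall bias". The section on independent assessment of the APP accepts that "it may be viewed as an intervention in itself, and have an unintended effect on study outcomes" and sets up a sub-study of 100 women followed without it. Under Statistical analyses, "the rate of primary and secondary study outcomes will be compared between the main study group and small sub-sample", and the two groups are also compared on "Compliance rates in the ingestion of the intervention, and completeness and acceptability of data collected during daily and weekly follow-up".

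The recording differs by group. Under Intervention, APP users "will receive daily questionnaires collecting data on treatment intake, breast pain, infection symptoms and infant feeding". By contrast, "Women not using APProve-Lite will receive an 8-week calendar diary to record their daily responses, along with a weekly questionnaire accessed by an emailed web-link". The sub-study section adds that sachet intake and symptoms are ticked on this calendar and that the woman posts it back in a reply-paid envelope. Table 1 lists treatment compliance in the same row as the symptom items, collected daily by APP or calendar.

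One further measure comes from neither instrument: "The number of unused sachets will be collected by the research coordinator at the end of the 8-week period".

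Under Outcome measures, the primary outcome can be met either by a clinical diagnosis or by a combination of breast and systemic symptoms lasting at least 24 hours.

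**The concern.** The sub-study is meant to show whether the APP changes outcomes. For daily symptoms, the thing being evaluated is also the thing that records them. A posted calendar can be filled in after the event, and it contributes nothing if it is not returned. Two groups with the same true mastitis rate could therefore show different recorded rates. Equal recorded rates could equally hide an APP effect offset by a capture difference.

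The same applies to compliance if it is read from the daily records, which is the source Table 1 gives.

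For recall bias the difficulty is of another kind: nothing in the planned comparison sets a recalled report against one made at the time.

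At stake is what the sub-study may conclude about the APP, not whether the probiotic works.

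**Working it through.** The plan gives no expected difference or precision for the APP comparison, so there is no stated figure on this point to reproduce. The check sets the sources side by side and then illustrates the mechanism.

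**Sources by mode**

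| Quantity compared | APP group | Diary group | Same source in both? |
|---|---|---|---|
| Symptom-route mastitis | daily APP questionnaire | posted paper calendar | no |
| Clinical diagnosis of mastitis | source not stated | source not stated | not stated |
| Doctors' visits, medication | weekly, APP | weekly, emailed web-link | electronic in both |
| Compliance, per Table 1 | daily APP questionnaire | posted paper calendar | no |
| Compliance, unused sachets | coordinator's count | coordinator's count | yes |
| Recall bias | no measure | no measure | not applicable |

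The 2-month questionnaire goes to both groups. Under Follow-up it may be completed by post, web-link or APP, with non-APP women using the web-link.

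**Illustration for mastitis (capture figures assumed, not in the documents)**

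Average true rate over the two treatment arms under the planning values in Sample size: (18% + 9%)/2 = 13.5%. Suppose a share f of cases meets the outcome by symptoms only and the diary misses a share m of those. Then:

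- Recorded diary rate = true rate × (1 − f × m).
- With f = 0.3 and m = 0.3: 13.5% × (1 − 0.09) = 12.3%, against 13.5% if the APP misses none. The gap is 1.2 points with no APP effect.

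If instead the capture difference applied to every case, the apparent risk ratio would be the ratio of capture rates, whatever the true rate. With 95% capture by APP:

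- diary 90%: 0.95/0.90 = 1.06
- diary 80%: 0.95/0.80 = 1.19
- diary 70%: 0.95/0.70 = 1.36

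For scale, take the 100 as part of the 600, so 500 v 100 (an assumption). The 95% half-width for a difference at 13.5% is 1.96 × √(0.135 × 0.865 × (1/100 + 1/500)) = 7.3 points.

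**Illustration for compliance, if the daily records were used (all inputs assumed)**

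- *Blank days counted as not taken.* True intake 80% in both groups, 90% of days filled in by APP and 70% by diary: 0.80 × 0.90 = 72% v 0.80 × 0.70 = 56%. The APP looks 16 points better.
- *Only returned diaries analysed.* 70% returned, with 88% compliance among returners and 61.3% among the rest: 0.7 × 0.88 + 0.3 × 0.613 = 80% true. The diary group reads 88% against 80% by APP, so the APP looks 8 points worse.

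The direction therefore depends on how gaps are handled. A sachet count depends on neither instrument being filled in.

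**Recall bias**

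The comparisons listed under Statistical analyses are outcome rates, compliance, completeness and acceptability. None contrasts a recalled report with a contemporaneous one, and the article describes no use of entry times.

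**The case against.** The strongest reply is that a reader might infer that the APP's effect cannot be separated from recording at all. The documents do not support that.

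- The unused-sachet count comes from neither instrument and is not limited to either group, so compliance can be compared on equal terms.
- Clinical diagnosis alone meets the primary outcome.
- Doctors' visits and medication are collected weekly and electronically in both modes.
- Completeness and acceptability are properties of the instrument and belong in its own records.

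All of this stands, and it confines the mastitis concern to the symptom route.

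It can also be said that a condensed article need not name the source for each comparison. That is fair as to silence. Here, however, Table 1 does name a source for treatment compliance, and it is the one that differs by mode, while the sachet count is not linked to the comparison.

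A third reply is that a recording difference is itself one way the APP could bias outcomes, so comparing overall rates serves the stated purpose. It does so for the combined effect. It does not show whether the APP changed what happened to the women, which is what treating it as a possible intervention asks.

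The illustrated 1.2-point gap is also small against a half-width of 7.3 points. This stands: at that size the distortion would rarely decide the comparison alone.

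Finally, if calendars are back-filled, the two modes do differ in recall. But without entry times or a reference report, nobody can tell which entries were recalled, so the hypothesis stays untested.

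**Conclusion.** The point holds in a limited form. In the APP v diary comparison, a difference in symptom-route mastitis cannot be attributed to the APP as opposed to capture. Compliance is labelled as coming from the daily records although an independent count is already being collected. The recall-bias hypothesis has no measure in the protocol article.

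The size of any distortion cannot be derived from the documents. The figures above show only the mechanism and rest entirely on assumed capture, return and completion rates.

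A reader might also infer that the main trial result is biased. It is not affected by this point: sub-study women are randomised to probiotic or placebo as in the main study, and allocation is blinded in both modes. This is a worthwhile correction to a secondary sub-study and does not threaten the primary analysis.

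**What to change.** 1. **Compliance.** Name the unused-sachet count as the compliance measure for the APP v diary comparison, with the daily records as secondary. This costs a sentence, since the count is already collected. The downside is that it will be missing for women who do not return packs.
2. **Mastitis.** In this comparison, report clinically diagnosed mastitis, asked with the same items in both modes, separately from symptom-route mastitis. State in advance that a difference confined to the symptom route may reflect ascertainment. Because the 2-month form may itself be completed in the APP, this reduces the mode difference but does not remove it.
3. **Recall bias.** Delete it from the hypothesis. Otherwise report within-woman agreement between the 2-month questionnaire and the daily and weekly records, noting that calendar entries may be back-filled and so are an imperfect reference. The second option may need one or two items on an existing questionnaire.

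None of these changes touches allocation, treatment or the primary analysis.
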